## Abstract

**Background:**

Sickle cell disease (SCD) is the most common monogenic disorder in humans and occurs predominantly among individuals who identify as Black or African American in the United States. In earlier work, we found that developmental delays were present in more than 50% of children with SCD before the age of 3 years, yet none had been diagnosed or referred to intervention services. Children whose caregivers participated in a home-based caregiver education program demonstrated improved scores on standardized developmental measures. When developmental delays go unidentified, children miss a critical opportunity for intervention during a period of rapid neurological change. Yet few, if any, studies have described the incidence and severity of developmental delays among children with SCD compared to controls.

**Objective:**

The purpose of this study is to determine the incidence and severity of developmental delays in children with SCD under 3 years of age (aim 1), test a 12-month home-based Sickle Cell Collaboration for Child Development (SCCCD) intervention (aim 2), and conduct a mixed methods study to identify contextual determinants to prepare for future scaling of the SCCCD intervention across health care systems (aim 3).

**Methods:**

Consistent with American Academy of Pediatrics guidelines, children with SCD will be evaluated at 9, 18, and 30 months using the Bayley Scales of Infant Development, Fourth Edition, to determine the incidence of developmental delay over the first 3 years of life compared to demographically matched peers (n=100, aim 1). The SCCCD intervention, adapted from a pilot study, combines skilled occupational therapy, the Parents as Teachers curriculum, and SCD-specific caregiver education, delivered over 12 monthly home visits (n=25, aim 2). Interviews with caregivers who participated in and those who declined the intervention will identify contextual determinants (ie, facilitators and barriers) to inform future testing and broader implementation of the SCCCD (aim 3).

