Despite the high prevalence of developmental delay in this population, critical gaps remain. No study has prospectively characterized developmental trajectories across the first 3 years of life in children with SCD using a demographically matched comparison cohort and psychometrically robust assessment methods. Earlier work suggests that delays may worsen as children age [6,7,27], but this trajectory has not been rigorously evaluated. Additionally, no disease-specific intervention has been formally tested for infants and toddlers with SCD, and little is understood about the contextual factors that would support broader implementation of such a program. Because known environmental mediators of development—including socioeconomic status and disease severity—require comparison to well-matched peers, a prospective design with a demographically balanced comparison cohort is essential.

The purpose of this study is to determine the incidence and severity of developmental delays at 9, 18, and 30 months of age in children with SCD compared to demographically matched peers (aim 1); evaluate the effect of a 12-month, home-based SCCCD intervention on developmental outcomes in children with SCD (aim 2); and identify contextual determinants that facilitate or impede caregiver participation in developmental screening and home-based intervention, in preparation for future broader implementation (aim 3).

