### Participants

#### Aim 1: Incidence Cohort (n=100)

Children with SCD (n=50) under 9 months of age with all SCD genotypes and their caregivers will be recruited from the Sickle Cell Clinic at SLCH. Children without SCD (n=50) will be recruited as a comparison cohort and matched at the group level to the SCD cohort on the distributions of age, sex, race, socioeconomic status, and Area Deprivation Index [32], rather than paired individually. Group-level matching will be finalized after enrollment. Typically developing children will be recruited through SLCH general medicine, community early childhood centers, local pediatricians, public libraries, local early intervention providers, and faith-based organizations, using methods previously successful in this lab [33,34]. Children will be excluded if they have a diagnosis associated with developmental delay that is not attributable to SCD, or if the family is not English-speaking.

Caregivers of children with SCD will be approached by phone or following a regularly scheduled clinic visit. Interested caregivers will review the informed consent document with a member of the research team by phone, Health Insurance Portability and Accountability Act (HIPAA)–secure video call, or in person.

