### Procedures

Developmental evaluations will be conducted at 9, 18, and 30 months of age (±1 month) for children enrolled in both aim 1 and aim 2. Evaluations will take place in a dedicated child-friendly testing room on the Washington University School of Medicine campus, which has a padded floor, child-safe furniture, and space for caregivers to sit comfortably. Five accessible parking spots are reserved directly in front of the testing room, and the space is located within a 5-minute walk of public transportation. Visits will last approximately 60 to 90 minutes. Snacks will be provided to support child engagement during the evaluation, and caregivers will be compensated for their time and travel at each visit. Following institutional review board (IRB) amendment, evaluations may also be conducted in the family’s home for participants residing within the Greater St. Louis Metro area, in response to caregiver feedback regarding barriers to on-site attendance. Any changes are communicated to participants and shared with our community advisory board.

Demographic information and caregiver surveys will be collected using REDCap, a HIPAA-secure web-based data capture system, administered on a research tablet [36,37]. Survey data may also be completed by caregivers remotely via a secure web-link before or after the visit to reduce in-person visit burden. Assessors will be trained to maintain adherence to the evaluation protocol prior to data collection. Following each evaluation, the assessor will prepare a written summary report of the child’s developmental scores, review the results with the caregiver, and share the report with the child’s pediatrician and hematologist at the family’s request. If a developmental delay is identified (>1 SD below the mean), the research team will discuss the results with the caregiver and offer a referral to Early Intervention services, the federally funded, state-administered early intervention program available to eligible children under 3 years of age at no cost to families [38,39].

Retention strategies include SMS text message reminders prior to each scheduled visit; flexible scheduling, including early morning, evening, and weekend appointments; and reimbursement for parking or public transportation. Text message reminders have been effective in reducing visit cancelations in our prior work [20].

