## Results

A total of 128 caregivers have been approached, and 72 have consented. Of those, 13 participants withdrew because of time constraints, interest, or loss to follow-up. As of May 31, 2026, a total of 26 unique participants with SCD have participated in aim 1, and 24 unique participants participated in the comparison cohort. For aim 2 with the pilot intervention, 13 caregivers have been approached and 7 have consented, and 5 caregiver or child dyads have been enrolled and have participated. Two caregivers withdrew due to moving out of state or living outside of the intervention radius (>60 miles). Characteristics of participants to date are available in Tables 2 and 3. Enrollment data can be seen in Table 4.

**Table 2. T2:** Caregiver demographics.

Demographics	Sickle cell cohort (aim 1; n=26)	Typically developing cohort (aim 1; n=24)	Sickle cell cohort (aim 2; n=5)
Parental role			
Mother, n	23	22	5
Father, n	3	2	0
Age (y), mean (SD)	30.9 (7.4)	33.4 (5.0)	28.8 (7.9)
Age group (y), n			
20‐29	17	6	2
30‐39	5	15	3
40‐49	4	3	0

**Table 3. T3:** Child demographics.

Demographics	Sickle cell cohort (aim 1), n	Typically developing cohort^a^ (aim 1), n	Sickle cell cohort (aim 2), n
Gender			
Male	13	13	3
Female	13	11	2
Race or ethnicity			
White	0	15	0
Black or African American	25	7	5
Asian	0	1	0
More than one race	1	1	0
Hispanic	0	2	0
Area of Deprivation Index state values			
1‐4 (least deprived)	6	14	1
5‐7	6	5	2
8‐10 (most deprived)	14	4	2

a One participant is excluded in Area Deprivation Index due to being suppressed in the calculation. Values reflect interim enrollment.

**Table 4. T4:** Current study participant enrollment (May 31, 2026).

Enrollment	Sickle cell disease (aim 1)	Typically developing (aim 1)	Sickle cell disease (aim 2)
9 months	12	10	5
18 months	22	15	0
30 months	18	16	0
Total unique participants	26	24	5
Total approach	84	44	13
Total consent	35	37	7

Participants in aim 1 for the SCD cohort all identify as Black or African American; 7 participants in the comparison cohort identify as Black or African American, 15 identify as White, 1 identifies as Asian, and 1 identifies as more than one race.

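### Aim 1 names incidence of delay as its target, but the analysis described gives prevalence at each age, and 28 of 50 children so far lack the 9-month evaluation that incidence after 9 months would need

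*Protocol article*

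**What the plan says.** **Target.** The Abstract (Methods) says children with SCD will be evaluated at three ages "to determine the incidence of developmental delay over the first 3 years of life", compared with matched peers. The Introduction restates the purpose as to "determine the incidence and severity of developmental delays at 9, 18, and 30 months of age". The Participants section calls the aim 1 sample an incidence cohort.

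**Entry and schedule.** Under Participants, Aim 1: "Children with SCD (n=50) under 9 months of age with all SCD genotypes and their caregivers will be recruited". The comparison children are to be "matched at the group level to the SCD cohort on the distributions of age, sex, race, socioeconomic status, and Area Deprivation Index". The Procedures section sets evaluations at 9, 18 and 30 months, each within one month.

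**Analysis.** Measures defines delay as a Bayley-4 score more than 1 SD below the mean. Data Analysis, Aim 1, specifies mixed effects regression with time, group and time-by-group as fixed effects. Missing Data and Attrition says children with incomplete visits are analysed on available data. A mixed effects logistic model for binary outcomes appears only under Data Analysis, Aim 2.

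**Interim counts.** Table 4 in Results is dated May 31, 2026. Its first row reads "9 months 12 10 5", for aim 1 SCD, aim 1 comparison and aim 2 in that order.

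**The concern.** Incidence counts new cases among children known to be free of the condition at the start of the interval. The proportion delayed at a fixed age is prevalence: it pools delay that has just appeared with delay that has been present for some time. A model of outcomes by visit and group estimates the second quantity, and the Introduction's phrase about incidence at three fixed ages in effect describes it.

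If the plan is followed as written, prevalence would be published as incidence. Readers would take the 18- and 30-month figures as new delay, and this is also what a later trial would draw on when deciding when delay begins. The low 9-month count adds a second problem. For a child first seen at 18 or 30 months, no analysis of these data can tell whether a delay is new.

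**Working it through.** **Inputs (Results, Table 4, aim 1)**

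| | SCD | Comparison |
|---|---|---|
| 9 months | 12 | 10 |
| 18 months | 22 | 15 |
| 30 months | 18 | 16 |
| Unique participants | 26 | 24 |
| Consented | 35 | 37 |
| Approached | 84 | 44 |

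**1. The article's totals reproduce.** Approached 84 + 44 = 128; consented 35 + 37 = 72; participated 26 + 24 = 50; still needed 24 + 26 = 50.

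**2. The age rows count evaluations, not current stage.** SCD: 12 + 22 + 18 = 52, more than 26. Comparison: 10 + 15 + 16 = 41, more than 24.

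**3. Children without a 9-month evaluation.** SCD: 26 − 12 = 14 (53.8%). Comparison: 24 − 10 = 14 (58.3%). Together 28/50 = 56%.

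**4. Could the 28 be infants awaiting a first visit?** Mostly not. The article reports 13 withdrawals, and 72 − 13 = 59, so 9 consented children lie outside the 50 who participated. Without relying on that, the later rows alone set a floor: at least 22 − 12 = 10 SCD and 16 − 10 = 6 comparison children were seen later with no 9-month evaluation.

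**5. Who can show new onset after 9 months so far?** Only children with a 9-month and a later evaluation. Assume each unique participant has at least one evaluation.
- SCD: at least 22 children have a later visit, so at most 26 − 22 = 4 have only the 9-month one. That leaves 12 − 4 = 8 at the least and 12 at the most.
- Comparison: at most 24 − 16 = 8 have only the 9-month visit. That leaves 10 − 8 = 2 at the least and 10 at the most.

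These counts are before removing children already delayed at 9 months, whose number is not reported.

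**6. Best case at full enrolment.** If the 14 and 14 stay in and every further recruit has a 9-month evaluation: SCD 12 + 24 = 36 of 50; comparison 10 + 26 = 36 of 50 (72% each). If only the floor in step 4 applies, the ceilings are 50 − 10 = 40 and 50 − 6 = 44.

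**7. Target against model, with complete data.** Suppose all 100 children had all three visits. The time-by-group model would still return a mean score or a proportion delayed at each age in each group. Nothing in Measures, Data Analysis (Aim 1) or Missing Data and Attrition removes children already delayed or defines first onset. The mismatch therefore does not depend on steps 3 to 6.

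**8. How far the two quantities can differ (illustration, assumed rates).** Let p9 and p30 be the proportions delayed at 9 and 30 months, and assume no recovery. Incidence among children free of delay at 9 months is (p30 − p9)/(1 − p9). With p30 = 50%: p9 = 0% gives 50%; p9 = 20% gives 0.30/0.80 = 37.5%; p9 = 50% gives 0%. Prevalence at 30 months is 50% in all three cases.

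**The case against.** The strongest reply is that the Abstract's wording can be read as cumulative incidence from birth, so that delay already present at 9 months counts. Nothing in the article promises incidence after a delay-free 9-month visit, and the illustration above targets only that second quantity. This is fair. But the birth-to-30-months reading needs a rule for ever having been delayed, which the article does not give. For a child without a 9-month visit it also needs delay to persist once present, which the documents do not establish.

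A second reply is that an article may leave at-risk sets to an analysis plan not shown. That would excuse silence. Here both the target and the model are stated, and they do not match. No later document can supply 9-month evaluations that were not made.

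Third, the available-data rule and the promise to report missingness patterns already deal with incomplete visits. They let the model run, but they do not recover onset.

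Several stronger readings are tempting and should not be drawn:
- **That the missing visits are why the plan yields prevalence.** They aggravate a mismatch that exists with complete data.
- **That the entry rule was broken.** Table 4 gives no entry ages, so a child recruited on time who missed the 9-month window would look the same. The under-9-months rule is explicit only for the SCD cohort; for comparison children it is implied by age matching and the shared schedule.
- **That only about 23 SCD and 21 comparison children of 50 will end with a 9-month evaluation** (12/26 × 50 and 10/24 × 50). This extrapolates an interim snapshot with half the sample still to enrol; 36 per group is possible.
- **That late joiners came because of developmental concerns.** The article reports neither late joining nor motives.
- **That the trajectory rests largely on different children at different ages.** At least 22 + 18 − 26 = 14 SCD children have both later visits, and at least 8 of the 12 seen at 9 months were seen again.

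**Conclusion.** The point holds in this form: the stated aim 1 target is incidence, and the stated aim 1 analysis estimates prevalence, or mean scores, at each age. This follows from the text alone.

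The size of the added problem is 28 of 50 children (56%) without a 9-month evaluation as of May 31, 2026, with a floor of 10 SCD and 6 comparison children seen later without one. To date, only 8 to 12 SCD and 2 to 10 comparison children can contribute to incidence after 9 months. These two ranges, and the ceiling of 36 of 50 per group, assume that every participant counted has at least one evaluation; the ceiling also assumes that the 28 remain in the study.

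Neither of the changes listed under Protocol Adaptations (home evaluations and an added screener) concerns entry age, and the article does not explain the low 9-month count. Whether it reflects late entry or missed visits stays open. The change is worth making now because it alters what aim 1 can claim and costs little.

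**What to change.** 1. Restate the aim 1 target throughout (Abstract, Introduction, Participants) as the prevalence of delay at 9, 18 and 30 months by group. For the binary outcome, extend to aim 1 the mixed effects logistic model now given under aim 2.
2. Report incidence only among children evaluated and not delayed at 9 months, and state that denominator in each group.
3. Reconcile the under-9-months recruitment rule with Table 4: state for the 28 children whether they entered late or missed the visit, and report age at first evaluation.
4. Add a sensitivity analysis limited to children first evaluated at 9 months.

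The cost is rewording, one logistic model already in the plan, a subset analysis and a short account of entry ages. The downside is that any incidence figure will rest on a smaller subset, at most 36 per group before children already delayed at 9 months are removed, and will be correspondingly imprecise.

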**Results:**

This project has been approved by the Institutional Review Board at Washington University School of Medicine (202104034 and 202407080). As of May 31, 2026, a total of 50 participants (26 children with SCD and 24 typically developing children for the comparison cohort) have participated for aim 1. Aim 2 recruitment began in July 2025, and 5 caregiver/child dyads have participated so far. The study is expected to be completed by 2028.

**Conclusions:**

These findings will provide the first prospective characterization of developmental trajectories in children with SCD across the first 3 years of life and establish preliminary evidence for a disease-specific, home-based intervention to improve developmental outcomes in this underserved population. The results will directly inform a future randomized controlled trial of the SCCCD intervention.

## Introduction

Sickle cell disease (SCD) is the most common monogenic disorder in the United States and is associated with severe pain, frequent hospitalizations, stroke, and cognitive decline [1-3]. In the United States, SCD is identified at birth and occurs predominantly among individuals who identify as Black or African American, a racially minoritized group in the United States [4]. Children with SCD are at elevated risk for developmental delays, which can emerge as early as 9 months of age and most often affect communication and cognition [5,6].

The American Society of Hematology (ASH) and the American Academy of Pediatrics both recommend early, frequent developmental screening for children with SCD, with ASH guidelines citing prevalence estimates of developmental delay affecting 30% to 50% of children [6-11]. Despite these recommendations, screening in primary care settings is not standard [12]. Many providers do not feel confident overseeing health care for children with SCD and are therefore less likely to monitor for early, subtle developmental delays [13,14]. Further, children of racially minoritized groups are less likely to be diagnosed with delays even when objective assessment criteria are met [15], and many children with SCD are not referred to intervention services before the age of 3 years. Current practice falls short of both the ASH and American Academy of Pediatrics standards, representing a missed opportunity for timely intervention during a period of rapid developmental change.

Yarboi et al [16] proposed that developmental delays in SCD result from both biological and environmental factors, including the effects of SCD along with household income, caregiver education, and parenting knowledge. Intervention development must consider both physiological and environmental contexts as lower caregiver stress is associated with better cognitive function in children with SCD [16], and greater caregiver knowledge of development can reduce stress, strengthen the caregiving relationship, and improve the home environment [17-19]. Caregivers of children with SCD have expressed a preference for home-based services, citing convenience and accessibility [20]. For this population, well-implemented, higher-dosage, home-based interventions in the first 3 years of life offer the potential to improve cognitive development and reduce the developmental gap between children from lower- and higher-income households [21-24]. Building on this evidence, our laboratory adapted the Parents as Teachers (PAT) curriculum specifically for families of children with SCD. The PAT curriculum is evidence-based and focuses on supporting and engaging caregivers in the home environment to promote optimal early development for children 0 to 3 years of age [21].

In earlier work, we adapted the PAT curriculum and combined it with SCD education and individualized occupational therapy (OT) to monitor and address developmental delays (n=43) [20]. This multicomponent OT + PAT + SCD intervention, the Sickle Cell Collaboration for Child Development (SCCCD), was offered to families until the child aged out of the program at 3 years. Using the Bayley Scales of Infant Development, Third Edition [25], we found that 50% of children over 12 months of age with SCD had a developmental delay, yet none were receiving these therapy services [6]. Caregivers demonstrated greater than 75% adherence with scheduled visits [20], and children whose caregivers participated either maintained or improved their Bayley scores [26]. Caregivers of the youngest children (under 1 year) were the most likely to enroll, and approximately 12 to 13 monthly visits produced the observed developmental gains [20]. These findings indicate that developmental delay in SCD emerges early, is not solely attributable to biological disease burden, is shaped by the caregiving environment, and can be meaningfully modified with approximately 1 year of targeted intervention.

Despite the high prevalence of developmental delay in this population, critical gaps remain. No study has prospectively characterized developmental trajectories across the first 3 years of life in children with SCD using a demographically matched comparison cohort and psychometrically robust assessment methods. Earlier work suggests that delays may worsen as children age [6,7,27], but this trajectory has not been rigorously evaluated. Additionally, no disease-specific intervention has been formally tested for infants and toddlers with SCD, and little is understood about the contextual factors that would support broader implementation of such a program. Because known environmental mediators of development—including socioeconomic status and disease severity—require comparison to well-matched peers, a prospective design with a demographically balanced comparison cohort is essential.

The purpose of this study is to determine the incidence and severity of developmental delays at 9, 18, and 30 months of age in children with SCD compared to demographically matched peers (aim 1); evaluate the effect of a 12-month, home-based SCCCD intervention on developmental outcomes in children with SCD (aim 2); and identify contextual determinants that facilitate or impede caregiver participation in developmental screening and home-based intervention, in preparation for future broader implementation (aim 3).

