## Methods

### Study Design and Setting

This study is funded by the National Heart, Lung, and Blood Institute under a K23 award designated Independent Clinical Trials Not Allowed (K23HL161328), reflecting the determination by the National Institutes of Health that the proposed research does not constitute an independent clinical trial. Aim 1 is an observational cohort study, and aim 2 is a feasibility pilot intended to inform a future randomized controlled trial. Accordingly, this study was not registered on ClinicalTrials.gov. This study includes 3 aims with different designs, and we selected a reporting guideline for each. We follow the STROBE (Strengthening the Reporting of Observational Studies in Epidemiology) guideline for the aim 1 cohort [28], the TIDieR (Template for Intervention Description and Replication) for the aim 2 SCCCD intervention [29], and the COREQ (Consolidated Criteria for Reporting Qualitative Research) for the aim 3 interviews [30]. We report the protocol following the SPIRIT (Standard Protocol Items: Recommendations for Interventional Trials) 2025 statement [31]. Completed TIDieR and SPIRIT 2025 checklists are provided as Checklists 1 and 2, respectively.

Participants are recruited through Washington University School of Medicine and the Sickle Cell Clinic at St. Louis Children’s Hospital (SLCH), a regional hub for pediatric SCD care that follows over 400 children and receives approximately 25 newborns with SCD annually. For aim 1, we will recruit 100 children, 50 with SCD and 50 demographically matched peers, who will complete developmental evaluations at 9, 18, and 30 months with concurrent caregiver surveys. For aim 2, an additional 25 children with SCD will be recruited to participate in a 12-month home-visiting intervention. Caregivers of children enrolled in aim 2 may also be invited to participate in a qualitative interview as part of aim 3.

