#### Aim 3: Qualitative Interview Sample (n=35)

Up to 35 caregivers of children with SCD will be invited to participate in a semistructured interview. Participants will be drawn from three groups: caregivers who completed 6 or more SCCCD intervention visits, caregivers who completed fewer than 6 visits, and caregivers who declined the intervention. With the consent of the primary caregiver, additional caregivers may also be invited to participate. Recruitment will continue until thematic saturation is reached [35].

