For aim 2, a pediatric occupational therapist with training in the PAT curriculum will conduct 12 monthly home visits with each enrolled family following the 9-month baseline evaluation. Visit scheduling will allow for up to 15 to 18 months of delivery to accommodate missed visits and ensure all families receive equivalent intervention dosage. Visits will be documented using daily notes that capture completed activities, caregiver engagement, visit duration, and any SCD-related topics reviewed.

For aim 3, semistructured interviews will be conducted with up to 35 caregivers of children enrolled in aim 2. Interviews will be conducted by the method of the participant’s choosing (eg, phone, HIPAA-secure video call, or in person) and are expected to last approximately 30 to 45 minutes. Interviews will be audio-recorded and transcribed verbatim. Two research team members will review all transcripts for accuracy prior to analysis. Caregivers will be compensated for their time.

All data will be stored with 2 levels of password protection. Paper consent documents will be maintained in a locked cabinet in a locked office. Data will be accessible only to the research team.

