### Implementation Science Framework (Aim 3)

To identify determinants that influence caregiver participation in developmental screening and the SCCCD intervention, we will use a mixed methods (QUAL → quan) approach guided by the Consolidated Framework for Implementation Research 2.0 (CFIR) [56-58]. The CFIR is one of the most widely used frameworks for understanding contextual determinants in implementation research and has been recently updated with greater emphasis on including recipients of the intervention as key informants [56], making it well suited for a caregiver-centered inquiry.

Semistructured interviews will be conducted with up to 35 caregivers of children enrolled in aim 2, organized around 3 CFIR construct domains: outer setting (eg, health care system and community context), intervention characteristics (eg, acceptability and perceived fit of the SCCCD), and inner setting (eg, family and social support). We are confident that thematic saturation will be reached [35,59]. Qualitative themes from interviews will be integrated with quantitative participation data from aim 2—including visit completion rates, home visit duration, and family engagement—to provide a comprehensive characterization of the contextual determinants that facilitate or impede caregiver participation.

Interviews will be audio-recorded and transcribed verbatim. Two research team members will use an iterative inductive and deductive thematic analysis approach to review all transcripts and generate themes for a preliminary codebook [60]. The preliminary codes will be applied to 4 interviews using NVivo software (version 14; Lumivero) [61]; any deviations will be discussed, and the revised codebook will be applied to all remaining interviews [62]. Codes will be analyzed for themes, and participation data from aim 2 will be summarized [63,64].

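### Aim 3 sets out to explain participation in developmental screening as well as in the intervention, but its interview groups and participation data are built around the intervention alone

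*Protocol article*

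**What the plan says.** Aim 3 has two stated targets. The Introduction says it will "identify contextual determinants that facilitate or impede caregiver participation in developmental screening and home-based intervention". The section Implementation Science Framework (Aim 3) opens in the same sense: "To identify determinants that influence caregiver participation in developmental screening and the SCCCD intervention". The Abstract's Objective is narrower and leaves screening out: "identify contextual determinants to prepare for future scaling of the SCCCD intervention across health care systems".

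The interview sample, in the Participants section for Aim 3, comes from three groups: "caregivers who completed 6 or more SCCCD intervention visits, caregivers who completed fewer than 6 visits, and caregivers who declined the intervention". Other sections describe a narrower frame. Study Design and Setting says "Caregivers of children enrolled in aim 2 may also be invited to participate in a qualitative interview as part of aim 3". Procedures says "semistructured interviews will be conducted with up to 35 caregivers of children enrolled in aim 2", and the framework section says the same.

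On the quantitative side, the framework section states "Qualitative themes from interviews will be integrated with quantitative participation data from aim 2". The examples it gives are completion of visits, length of home visits and family engagement.

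**The concern.** A study of why families do or do not take part needs to hear from some who did not. For the intervention, the plan provides this: the three groups run from high attendance through low attendance to refusal. For screening there is no such range. No group is defined by refusing, missing or leaving the developmental evaluations, and evaluation attendance is not named among the data to be integrated.

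Accounts of screening would then come mostly from families who had already managed to attend. The hardest barriers, those that kept families away altogether, would be under-represented. The team has reason to want this information, because Procedures and Protocol Adaptations record that evaluations were opened to the home after caregivers reported barriers to attending on site.

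**Working it through.** Aim 3 has no power or sample-size calculation to reproduce. The check sets objective against design, then uses subtraction on Table 4.

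**Objective against design**

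| Element | Screening | Intervention |
|---|---|---|
| Objective (Introduction; Implementation Science Framework) | named | named |
| Objective (Abstract) | not named | named |
| Interview groups (Aim 3 sample) | no group defined by it | all three groups defined by it |
| Interviewees (Study Design, Procedures, Framework) | Aim 2 enrollees | Aim 2 enrollees |
| Quantitative strand (Framework) | not named | Aim 2 participation data |

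Under Aim 2: Intervention Cohort and Procedures, home visits follow the 9-month baseline evaluation. Anyone in the two visit-count groups who has begun home visits has therefore attended at least one evaluation. The third group is selected for declining the intervention, and the article does not say whether that refusal comes before or after an evaluation.

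**Are the data recorded elsewhere?** Yes. Data Analysis records the number of evaluations completed (Aim 1) and the caregivers approached and enrolled (Aim 2). Missing Data and Attrition records missed evaluations across all aims. Table 4 gives approach and consent counts. None of these is tied to Aim 3.

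**Size of the group not sampled by design (Table 4, interim, 31 May 2026)**

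The Results text says "A total of 128 caregivers have been approached, and 72 have consented". The two Aim 1 columns of Table 4 reproduce this: 84 + 44 = 128 approached and 35 + 37 = 72 consented. These totals are therefore Aim 1 only. For the SCD cohort:

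- Approached without recorded consent: 84 − 35 = 49, and 49/84 = 58%.
- Consented but not counted as participants: 35 − 26 = 9, and 9/35 = 26%.
- Together: 49 + 9 = 58, and 58/84 = 69%, an upper bound.

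The 9 cannot be resolved further. Over both cohorts 72 − 50 = 22 consenters are not among the 50 participants, while 13 withdrawals are reported. If all 13 fall among those 22, 9 remain unexplained and may be pending. The comparison cohort's own gap is 37 − 24 = 13, so between 0 and 9 of the SCD cohort's 9 could be withdrawals.

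For Aim 2, 13 − 7 = 6 approached caregivers have no recorded consent, and 7 − 5 = 2 withdrew.

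Table 4 also lists 22 SCD children at 18 months but only 12 at 9 months. If the rows count completed evaluations, at least 22 − 12 = 10 children were evaluated at 18 months without a 9-month evaluation. The article does not say whether those visits were missed or the children entered late.

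**The case against.** The strongest reply is that screening is not left out. Aim 2 children are due for evaluation at 9, 18 and 30 months, so their caregivers can be asked what helped or hindered attendance, and some will miss a later visit. The framework's outer- and inner-setting domains bear on screening as much as on home visits. Infants are recruited to Aim 2 before 9 months, so a caregiver who declines the intervention may have declined the evaluation too. An Aim 1 decliner could also be approached later for Aim 2, decline again and enter the third group. The list of participation variables is worded as open-ended, and attendance is recorded. Qualitative work does not need a planned contrast for every behaviour studied.

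Much of this stands. A reader might infer that the screening half of Aim 3 cannot be answered, or that non-attenders can never be reached. The documents do not support either reading, because both routes just described remain open.

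Three further inferences should also be resisted. The 69% is not a refusal rate: the article does not say how many of the 49 refused, were pending, were ineligible or were not reached. Declining a research cohort is not the same as declining screening in care. The statement in Conclusions about informing screening recommendations refers to the results of the whole study, and Aim 1's incidence and severity data could support it without Aim 3.

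What the reply does not remove is the selection. Non-attenders can enter by chance, but no one is chosen for that reason. The list of variables may be open, but its stated source is Aim 2. Nor is this detail left to a fuller document: the article states its groups and data source, and they do not match its stated objective.

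**Conclusion.** The concern holds as a mismatch between a stated objective and the design meant to meet it. The screening target is addressed only incidentally and mainly through families who attended at least the 9-month evaluation. Barriers to screening are therefore likely to be understated. The direction of this bias rests on the assumption that families who stay away face more or different barriers than those who attend. Its size cannot be computed from the article.

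The pool not sampled by design is at most 58 of 84 approached SCD families in Aim 1 to date (49 without recorded consent plus 9 consenters not counted as participants). The true number of non-participants may be well below that. The intervention half of the aim is unaffected, apart from the inconsistency over whether intervention decliners are interviewed. The point is moderate and easily corrected.

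**What to change.** 1. In Implementation Science Framework (Aim 3), add the approach, consent and evaluation-attendance data for SCD families in Aims 1 and 2 to the quantitative strand. These data are already recorded, so the cost is close to nil.

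2. Then choose one of two routes:
   - Within the ceiling of 35 interviews, purposively include caregivers of children with SCD who declined, missed or withdrew from evaluations. This means fewer interviews per intervention group and an IRB amendment. The timing is favourable, since 20 of the 25 Aim 2 participants are still to be recruited.
   - Or remove developmental screening from the Aim 3 objective in the Introduction and the framework section, and limit Aim 3's conclusions to participation in the SCCCD intervention, as the Abstract's Objective already does. This costs only an edit.

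3. In the same edit, reconcile the sampling frame. The Aim 3 sample section and the Abstract's Methods include caregivers who declined the intervention. Procedures and the framework section describe interviewees as caregivers of Aim 2 enrollees, and Study Design and Setting mentions no others.
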